### Study Setting

In this multicenter study, we aim to recruit all patients between July 2025 and August 2027 in the Sports Medicine Division of La Providence Hospital and in the Rehabilitation division, Hôpital Fribourgeois, both in Switzerland. The lead center is the Sports Medicine Division of La Providence Hospital where author AS is the sponsor-investigator. All the interventions will be performed in the lead center.

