Postintervention care includes (1) partial weight-bearing for 1 month; (2) active strengthening of the muscles without overloading the knee using, if possible, the blood-flow restriction technique and gentle nonweight-bearing muscle activation, including core stability exercises; (3) mobility; and (4) modification of daily activities, work, and sports habits.

A total of 5 follow-up visits are planned for the study, during which principal and secondary outcomes will be gathered by a blinded investigator. At the 1-month and 2-month follow-up visits, patients in both study arms will receive 2 additional ultrasound-guided PRP injections performed by the blinded investigator and following the same Arthrex autologous conditioned plasma technique. The same postintervention care will be provided after these 2 PRP injections. Figure 1 shows the study flow chart.

Anticoagulants (eg, aspirin) and anti-inflammatory drugs (eg, ibuprofen, naproxen, meloxicam) should not be used 2 weeks before and 2 weeks after each injection as it can potentially interrupt the therapeutic acute inflammatory response and cytokine production.

Active physical therapies regimens, orthotics use, sports, and daily activities are adapted to the patient, on a day-by-day basis, during the postintervention care.

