### Randomization and Blinding

Study participants will be randomized at a 1:1 ratio to either the intervention arm or the active comparator arm using a randomization table and blocked randomization with blocks of 4 patients. Participants will be assigned to specific strata based on age (older or younger than 40 years) and the presence of cartilage defects (partial, full, or full with bone deformation).

The unblinded investigator responsible for the study interventions will perform the randomization shortly before administering the interventions. This study is triple-blinded: (1) Participants will be unaware of their group assignment throughout the intervention and study duration, (2) the investigator performing the intraarticular injection and the outcome assessor will remain blinded, and (3) the statistician will also be blinded. The investigator responsible for preparing the PRP+SVF or PRP-only preparation will be unblinded and will not participate in outcome assessments.

All patients will undergo a venipuncture, either a lipoaspirate or a sham lipoaspirate, followed by an ultrasonographically guided PRP or PRP+SVF injection. It is anticipated that unblinding will not be required to ensure patient safety, as no known adverse effects of the SVF (such as local pain, tenderness, hematoma on donor site, or infection) require unblinding for clinical management. However, if unblinding becomes necessary due to unexpected circumstances, the unblinded investigator will disclose the allocated intervention for the affected patients.

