### Statistical Analysis

The WOMAC score will be normalized to a 0%-100% scale, where 0% indicates no symptoms and 100% represents the highest severity of symptoms. This normalization involves converting the raw scores into percentages, facilitating the interpretation and comparison of results across participants and study groups. The absolute difference at 6 months will serve as the primary outcome and will be compared using either the paired Student *t* test or the Wilcoxon signed-rank test, depending on the distribution of the variable, with intention-to-treat analysis. The absolute differences in secondary outcomes (changes from baseline to other time points) between the treatment and control groups will be evaluated with the appropriate statistical test (categorical variables: chi-square or Fisher exact tests; continuous variables: Student *t* or Wilcoxon rank tests). All analyses will include both intention-to-treat and per-protocol analyses. Effect estimates, 95% CIs, and descriptive *P* values will be reported whenever possible, along with corresponding graphs.

A post hoc analysis will attempt to identify variables of interest using the appropriate global linear model.

Since the intervention is considered low risk, no interim analysis is planned. In case of missing primary outcome data, patients will be withdrawn from the analysis. Patients missing secondary outcome data will remain in the study but be excluded from those specific analyses.

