The meta-analysis by Lee et al [19] showed some differences between both therapies on clinical outcomes. A significant improvement in the VAS score was found at 6 months and 12 months with AD-MSCs (6 months: MD=–1.62, 95% CI –2.46 to –0.79; 12 months: MD=–1.97, 95% CI –3.22 to –0.72), whereas SVF showed significant results only at 12 months (6 months: MD=–2.32, 95% CI –5.15 to 0.52; 12 months: MD=–2.13, 95% CI –3.06 to –1.21). In contrast, functionality measured with WOMAC scores improved significantly 6 months after SVF treatment (MD=–6.12, 95% CI –10.71 to 1.52), while AD-MSC therapy yielded significant improvements only after 12 months (6 months: MD=–1.96, 95% CI –5.36 to 1.45). At 12 months and 24 months, both SVF and AD-MSC therapies produced significant improvements in the WOMAC score (12 months SVF: MD=–9.09, 95% CI –12.67 to –5.51; 12 months AD-MSC: MD=–9.19, 95% CI –12.48 to –5.90; 24 months SVF: MD=–10.71, 95% CI –18.49 to –2.93; 24 months AD-MSC: MD=–6.88, 95% CI –10.24 to –3.52).

The first main strength of our study design is the large sample size. Second, our study population is well-designed and reproducible, with standardized diagnostic criteria and failure of a first-line standardized rehabilitation plan. Third, the multicenter design allows for better reproducibility of patient selection and management, even if interventions are performed at the main study center by a single investigator. This is, however, a study strength, as it will avoid bias related to the intervention techniques.

A sham lipoaspiration procedure with the patient awake is performed to maintain blinding in the control group. Despite all precautions taken to uphold allocation concealment, breaches may occur if the patient diligently questions the procedure. For ethical reasons, if at 6 months, the progression is unsatisfactory, the intervention's nature may be disclosed if deemed clinically relevant, allowing the patient to benefit from SVF infiltration. Consequently, the study may be limited, as the initial 12-month secondary outcomes will not be considered in the final analysis. Finally, the patient selection, clinical follow-up, and rehabilitation plan might differ across the various recruitment centers (multicenter design).

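### The primary 6-month WOMAC comparison leaves out recruiting centre, although the protocol expects that centres might differ; the cost is some precision, not bias

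*Protocol article*

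**What the plan says.** Patients are recruited "in the Sports Medicine Division of La Providence Hospital and in the Rehabilitation division, Hôpital Fribourgeois, both in Switzerland" (Study Setting), and the same section adds: "All the interventions will be performed in the lead center". Randomization and Blinding describes 1:1 allocation "using a randomization table and blocked randomization with blocks of 4 patients" and says: "Participants will be assigned to specific strata based on age (older or younger than 40 years) and the presence of cartilage defects". Nothing stated there makes the allocation list specific to a centre.

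Statistical Analysis says that the primary outcome, the absolute difference in normalised WOMAC at 6 months, "will be compared using either the paired Student *t* test or the Wilcoxon signed-rank test, depending on the distribution of the variable". No covariate is named. The only model in that section comes afterwards: "A post hoc analysis will attempt to identify variables of interest using the appropriate global linear model".

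Interventions gives one list of post-intervention care for both arms and then says: "Active physical therapies regimens, orthotics use, sports, and daily activities are adapted to the patient, on a day-by-day basis". Among the limitations, the Discussion says that "the patient selection, clinical follow-up, and rehabilitation plan might differ across the various recruitment centers". The preceding paragraph counts the multicentre design as a strength because it should make selection and management more reproducible.

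**The concern.** The recruiting divisions are of different types, one in sports medicine and one in rehabilitation. The protocol itself says that the patients they select, and the rehabilitation those patients follow, might not be alike. Both could plausibly affect a functional score at 6 months. Centre is known for every patient before randomisation, so it is an obvious baseline factor to use, and the stated primary comparison does not use it.

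Two things follow if the centres do differ. The between-centre spread stays in the residual variance, so the confidence interval is wider than it needs to be. In the one trial that is run, the arms may also hold different shares of the two centres' patients, and the estimate moves accordingly. If an imbalance is then seen, the only adjustment on offer is a post hoc model with unnamed variables, chosen after the data are known.

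**Working it through.** **Inputs from the protocol (Sample Size).** Difference 9.1 points, SD of change 13.9, 54 per arm, two-sided 5%, 90% power. Statistical Analysis names paired tests, which is a separate matter; the comparison is read here as between groups, as in Sample Size.

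**Assumed, because the documents do not say.** The second centre's share of patients (50%, with 20% and 30% as alternatives) and the gap D between centres in mean WOMAC change (3, 5 or 9.1 points).

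**1. The plan's own figure.** n per arm = 2 × (1.960 + 1.282)² × 13.9² / 9.1² = 49.0, which the calculation rounds up to 50 (100 in total). The exact t calculation gives 51 (102 in total). The stated 108 is not reproduced. At 54 per arm power is 0.925 (normal) or 0.921 (exact t), so the deviation is conservative and does not affect this point.

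**2. Standard error as planned.** 13.9 × √(2/54) = 2.68.

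**3. Share of variance due to centre**, with 13.9 as the total SD and equal centres: D² × 0.25 / 13.9².
- D = 3: 2.25 / 193.2 = 1.2%
- D = 5: 6.25 / 193.2 = 3.2%
- D = 9.1: 20.7 / 193.2 = 10.7%

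With 20% at the second centre, 0.25 becomes 0.20 × 0.80 = 0.16. The shares at D = 5 and 9.1 are then 2.1% and 6.9%.

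**4. Standard error after adjusting for centre** (equal centres): 2.68 × √(1 − share).
- D = 5: 2.63, an interval 1.6% narrower
- D = 9.1: 2.53, an interval 5.5% narrower

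**5. Chance imbalance.** The SD of the between-arm difference in centre share is √(0.5 × 0.5 × 2/54) = 0.096. The 95% range of the resulting shift in the estimate is ±1.96 × 0.096 × D:
- D = 5: ±0.94 points
- D = 9.1: ±1.72 points

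This shift is already inside the planned standard error. For D = 9.1 its SD is 0.096 × 9.1 = 0.88, and 2.53² + 0.88² = 6.4 + 0.8 = 7.2 = 2.68². It must not be added to 2.68 a second time.

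**6. Simulation check.** There were 40,000 trials per scenario, with 54 per arm, centre ignored in the allocation and the stratum blocks not modelled. Here 13.9 is the SD within centre and the gap is added on top, which is less favourable than step 3. Ranges are over second-centre shares of 20%, 30% and 50%.

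| Assumed gap | 95th percentile of shift (points) | Power, centre ignored | Power, centre in model |
|---|---|---|---|
| 0 | 0 | 0.921–0.922 | 0.918–0.920 |
| 3 | 0.4–0.6 | 0.916–0.918 | 0.916–0.919 |
| 5 | 0.7–0.9 | 0.913–0.917 | 0.919 |
| 9.1 | 1.4–1.7 | 0.894–0.903 | 0.916–0.919 |

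The shift averages zero in every scenario. Type I error is 0.048 to 0.051 with or without centre in the model.

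**The case against.** The case for leaving the plan alone is strong in several respects.

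- **Validity.** A reader might infer that centre imbalance distorts the treatment effect. It does not. Under randomisation the imbalance has mean zero, the standard error already contains it, and type I error holds at 5%. This stands in full.
- **Assumed drivers.** No centre gap or centre share is given, and 9.1 points is simply the trial's target difference borrowed as an upper case. This stands, which is why the size is given as a range. At a 3-point gap the effect is negligible.
- **What the text admits.** A reader might take the Discussion to say that care does differ by centre. It says only that it might. The day-by-day adaptation in Interventions is to the individual patient, and a centre term would not remove it. All injections take place at the lead centre, by a single investigator according to the Discussion, so differences in technique between sites do not arise.
- **Stratification.** A reader might conclude that centre should become a stratum. The present strata give 2 × 3 = 6 cells. Adding centre gives 12, or 108/12 = 9 patients per cell on average with blocks of 4, and some cells would probably be sparse. Leaving centre out of the strata is a defensible choice.
- **Unseen analysis plan.** Covariates are often left to a statistical analysis plan, which might add centre. This stands only in part. The article states a specific primary test without covariates and assigns modelling to a post hoc step, so adding centre would change a stated method.

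**Conclusion.** The point holds as a minor matter of efficiency and prespecification. The protocol foresees possible differences between its two recruiting centres and states a primary comparison that ignores centre. The inference remains valid.

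With equal centres, a total SD of 13.9 and an assumed gap of 5 to 9.1 points, the unadjusted interval is about 2% to 6% wider than the adjusted one. If the gap is added on top of 13.9, the loss is at most 2 to 3 power points, and only at the 9.1-point gap; power still stays near the planned 90%. In a single trial the estimate could move by about 1 to 2 points in the more extreme assumed cases, against a target of 9.1. Smaller gaps, or unequal centres in step 3, make the gain from adjustment smaller.

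**What to change.** Keep the present strata. State in Statistical Analysis, before any data are seen, that recruiting centre is a factor in the primary between-group analysis of 6-month WOMAC change: a linear model with arm and centre or, if the non-parametric route is taken, a centre-stratified rank test. The post hoc model can then stay exploratory and need not carry this adjustment.

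The cost is one degree of freedom (105 residual instead of 106) and no extra patients or data. If the centres turn out not to differ, the simulated power changes from about 0.922 to 0.919 with equal centres. Centre need not be added as a randomisation stratum.

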## Appendix

Multimedia Appendix 1 Participant Screening Case Report Form (CRF).

Multimedia Appendix 2 Participants Enrollment Case Report Form (CRF).

Multimedia Appendix 3 Participants Follow-up Case Report Form (CRF).

Multimedia Appendix 4 Averse Events and Serious Adverse Events Case Report Form (CRF).

Multimedia Appendix 5 Patients informed consent.

## Abbreviations

AD-MSC: adipose-derived mesenchymal stem cells
AE: adverse event
AMADEUS: Area Measurement and Depth and Underlying Structures
B-MSC: bone marrow–derived mesenchymal stem cells
CONSORT: Consolidated Standards of Reporting Trials
CRF: case report form
ICH: International Council for Harmonisation
MD: mean difference
MOCART: Magnetic Resonance Observation of Cartilage Repair Tissue
MRI: magnetic resonance imaging
MSC: mesenchymal stem cell
NSAID: nonsteroidal anti-inflammatory drug
PRP: platelet-rich plasma
RCT: randomized controlled trial
SAE: serious adverse events
SVF: stromal vascular fraction
VAS: visual analog scale
WOMAC: Western Ontario and McMaster Universities Osteoarthritis Index
WORMS: Whole-Organ Magnetic Resonance Imaging Score
